#### Descriptive statistics

Baseline demographic and clinical characteristics will be summarized by treatment group. Continuous variables will be presented as mean ± standard deviation (SD) or median (interquartile range, IQR) depending on their distribution. Categorical variables will be presented as frequencies and percentages. No formal statistical comparisons of baseline characteristics will be performed, consistent with CONSORT recommendations for randomized trials.

#### Primary outcome analysis

The primary outcome measure—the change in the number of days with moderate-to-severe headaches per menstrual cycle from the last menstrual cycle of the screening period through the end of the 3-month intervention—will be analyzed using a repeated-measure mixed-effects model (MMRM). This model will treat the measurements from each menstrual cycle during the 3-month intervention period as repeated measures, with treatment group, time, and the interaction between treatment and time as fixed effects. The average number of moderate-to-severe headache days from the qualified screening cycles will be included as a covariate, and subject-specific random intercepts will be specified to account for within-subject correlation across the three menstrual cycles.

The primary focus is on the differences in the magnitude of change from baseline across groups at the end of the intervention period (Week 12/Month 3). Results will be presented as adjusted between-group differences, along with their 95% confidence intervals (CI) and corresponding *p*-values. Given that this is a preliminary feasibility study, *p*-values will be interpreted descriptively rather than as confirmatory evidence.

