### Eligibility criteria

#### Inclusion criteria

Meets the diagnostic criteria for “migraine without aura” (ICHD-3 code 1.1)” as defined in the International Classification of Headache Disorders, 3rd Edition (ICHD-3);Meets the diagnostic criteria for “pure menstrual migraine” (A1.1.1) or “menstrually-related migraine” (A1.1.2) as outlined in the appendix to the ICHD-3, and this diagnosis has been validated by a prospective headache diary covering three consecutive menstrual cycles;Age 18–45 years, with a normal menstrual cycle of 28 ± 7 days and a menstrual duration of 3–7 days;During the 3-cycle screening period, at least 2 of the 3 menstrual cycles have 2–14 days with moderate-to-severe headache (NRS ≥ 4) per cycle (meeting the ICHD-3 appendix criterion for PMM or MRM). Baseline data for the primary outcome will be calculated as the average number of moderate-to-severe headache days across all qualified cycles (i.e., those cycles meeting the 2–14 day criterion) during the screening period;Complete the daily headache diary throughout the 3-cycle screening period (with a completion rate of ≥80% for daily entries within each menstrual cycle) to demonstrate good patient compliance;Voluntary signing of the informed consent form.

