### Primary outcome

The primary outcome measure is the change in headache frequency, defined as:

Measurement: The mean change in the number of moderate-to-severe headache days per menstrual cycle from baseline (defined as the average across all qualified cycles during the 3-cycle screening period) to the end of the 3-month intervention period. Definition: A headache day is defined as any calendar day on which the participant experiences a headache meeting ICHD-3 criteria for migraine without aura (ICHD-3 code 1.1) with a peak pain intensity of ≥4 on the 0–10 Numeric Rating Scale (NRS, where 0 = no pain, 1–3 = mild, 4–6 = moderate, and 7–10 = severe; thus an NRS score of ≥4 captures both moderate and severe intensity levels). Data Source: Prospectively captured using a validated, electronic daily headache diary.

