Randomization: Eligible participants who have completed the screening period and whose prospective diary data confirm the diagnosis of PMM or MRM (i.e., at least 2 of the 3 screening cycles meet the predefined headache frequency criterion of 2–14 moderate-to-severe headache days) will be randomly allocated in a 1:1 ratio to the press-needle group or the naproxen sodium group. Participants who do not meet this diagnostic confirmation will be excluded from randomization. Baseline values for the primary outcome will be derived from the average of all qualified screening cycles (those with 2–14 moderate-to-severe headache days), ensuring that the baseline reflects the participant’s typical headache burden rather than a single potentially atypical cycle.

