#### Plans for collection, laboratory evaluation and storage of biological specimens for genetic or molecular analysis in this trial/future use

Peripheral venous blood samples (10 mL) will be collected at four predefined timepoints early follicular phase (menstrual days 2–4) and mid-luteal phase (approximately 7 days before the next expected menstruation) during the last (third) menstrual cycle of the screening period (serving as the baseline samples), and again at the same two phase-specific timepoints during the final (third) treatment cycle (post-intervention samples). Samples will be processed within 30 min to obtain serum and plasma aliquots, which will be stored at −80 °C in a designated biobank. In the current trial, these specimens will be analyzed for pre-specified biomarkers [calcitonin gene-related peptide (CGRP), estradiol (E2), and progesterone (P4)] using validated commercial assay kits. The baseline biomarker data will be derived from samples collected during the last screening cycle and will be temporally aligned with the baseline headache diary data (derived from the same cycle after diagnosis confirmation). With separate, explicit participant consent, de-identified leftover samples may be retained for future ethically approved research on headache disorders. A secure, coded system will protect participant confidentiality, and participants may withdraw consent for future use at any time.

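### The primary-outcome baseline is defined in two incompatible ways: the last screening cycle, and the mean of the qualified screening cycles

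*Protocol article*

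**What the plan says.** Two definitions are in force.

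**Last screening cycle.** Under "Primary outcome analysis" the endpoint is "the change in the number of days with moderate-to-severe headaches per menstrual cycle from the last menstrual cycle of the screening period" to the end of treatment. The section on biological specimens, which takes baseline blood in the third screening cycle, says the biomarker data "will be temporally aligned with the baseline headache diary data (derived from the same cycle after diagnosis confirmation".

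**Mean of qualified cycles.** The inclusion criteria say baseline is "calculated as the average number of moderate-to-severe headache days across all qualified cycles (i.e., those cycles meeting the 2–14 day criterion". The "Primary outcome" section measures change "from baseline (defined as the average across all qualified cycles during the 3-cycle screening period". "Recruitment process" repeats this under both diagnostic confirmation and randomization, and gives the reason: baseline should reflect the "typical headache burden rather than a single potentially atypical cycle".

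The analysis section then enters the qualified-cycle mean as the model covariate, so both definitions stand in one paragraph. A woman is eligible if at least two of her three screening cycles qualify. She can therefore be randomised with one cycle outside the 2–14 day range.

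**The concern.** A non-qualifying third cycle is excluded from baseline under one definition and is the whole of baseline under the other. The recruitment section also rejects reliance on a single cycle, which is what the analysis and specimen sections do.

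The "Sample size" section says the trial exists to estimate the effect size and variance of the primary outcome for a definitive trial. If that variance depends on which section the analyst follows, so does the next trial's sample size.

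A second, smaller issue concerns the qualified-cycle mean itself. It removes screening cycles because of their headache count, while every treatment cycle counts whatever its value. Change within an arm is then measured from a selected baseline to an unselected follow-up.

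**Working it through.** **1. The plan's own figure.** 30 evaluable per arm with 20% dropout: 30 / 0.80 = 37.5, rounded up to 38; 2 × 38 = 76. This reproduces. No figure is given for headache days per cycle.

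**2. Invented example.** Screening counts 5, 4, 1 and a Month 3 count of 3. She is eligible (two of three cycles in range).
- Last cycle: baseline 1, change 3 − 1 = +2.
- Qualified mean: (5 + 4) / 2 = 4.5, change 3 − 4.5 = −1.5.
- All three cycles: 10 / 3 = 3.33, change −0.33.

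The same diary gives a worsening or an improvement.

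**3. Why the mixture costs precision.** Let Y be the Month 3 count, L the last-cycle count and B the qualified mean. Analysing Y − B with B as covariate gives the same treatment estimate as analysing Y with B as covariate, with residual variance Var(Y|B). Analysing Y − L with B as covariate gives Var(Y|B) + Var(L|B) − 2Cov(Y, L|B). The part of L that B does not explain stays in the outcome as noise.

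**4. Simulation, no treatment effect and no time trend.** Assumptions, none from the documents: subject means gamma with shape 2, 4 or 6.25 (CV 0.71, 0.50, 0.40); cycle counts Poisson or negative binomial (k = 4); population means 3, 4, 5, 6 and 8 days. The protocol's eligibility rule was then applied. Precision was taken from a Month 3 regression on baseline, standing in for the Month 3 contrast of the repeated-measures model. Ranges cover the six scenarios at each mean.

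| Assumed mean | Qualified mean minus later cycle | All-three mean minus later cycle | Extra residual variance, mixed baselines |
|---|---|---|---|
| 3 | +0.49 to +0.88 | +0.18 to +0.34 | 47–60% |
| 4 | +0.30 to +0.60 | +0.10 to +0.21 | 44–55% |
| 5 | +0.01 to +0.27 | +0.01 to +0.09 | 41–52% |
| 6 | −0.30 to +0.06 | −0.12 to +0.01 | 39–50% |
| 8 | −0.91 to −0.20 | −0.37 to −0.09 | 36–47% |

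A positive difference appears as improvement without any treatment effect; a negative one as worsening.

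Across all scenarios:
- The two baselines differ by at least one day in 54–77% of eligible women.
- One screening cycle is dropped in about 17–53%, and the last cycle is itself non-qualifying in about 6–18%.
- The standard error ratio is √1.36 = 1.17 to √1.60 = 1.26. In precision, 38 per arm becomes worth 38 / 1.60 = 24 to 38 / 1.36 = 28.
- Using the all-three mean for both roles gives 1–8% less residual variance than using the qualified mean for both.

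**5. Between-arm contrast.** 4,000 null trials, 38 per arm, mean 4, CV 0.40, k = 4. The adjusted difference averaged 0.02 days under either version, against Monte Carlo errors of 0.75 / √4000 = 0.012 and 0.93 / √4000 = 0.015, so it is compatible with zero. The standard error was 0.75 with one baseline and 0.93 with the mixture: 0.93 / 0.75 = 1.24, or about 23% larger before rounding.

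**The case against.** **The analysis wording may mark a time span rather than a baseline.** Taken alone, that is possible. The specimen section removes the doubt, because it says outright that the baseline diary data come from the same cycle as the blood samples.

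**The qualified-cycle mean clearly prevails.** It does, and applying it in the two outlying places would cure the contradiction. Moving to all three cycles is a preference beyond that cure, and it replaces a definition the authors gave reasons for.

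**The trial is exploratory.** P-values are to be read descriptively, and the statistician works on coded groups until the pre-specified analyses are complete. A reader might infer that the endpoint could be chosen to favour an arm. The coding lowers that risk, but it does not settle which endpoint is meant.

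**Selection on the outcome.** A reader might infer that the qualified-only mean inflates baseline and so flatters the treatment. The documents do not support this in two respects. The rule is applied before randomisation, identically in both arms, so it does not bias the between-group difference that the protocol makes its focus. Nor is the direction fixed: the rule drops cycles above 14 days as well as those below 2, and without a mean in the documents the sign is unknown. No within-group test of headache days is planned either. What stands is that within-arm change and the reported baseline level are distorted if used for planning.

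**Precision.** A reader might blame a weak single-cycle covariate. The protocol's covariate is the qualified mean; the loss comes from pairing it with a different baseline in the change score.

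**Conclusion.** The contradiction is certain and needs no assumption: the primary endpoint has two baselines, and the analysis paragraph uses both. It should be fixed before any analysis.

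Its size depends on the simulation assumptions. Over the range run, the analysis as written has about 36–60% more residual variance than one baseline used throughout, which undermines the variance estimate that the pilot is meant to deliver. The treatment comparison is less precise but unbiased.

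The selection effect is secondary and conditional. The qualified-only mean overstates within-arm improvement at assumed means of about 3–5 days per cycle (though almost nil in one scenario at 5), is mostly near nil around 6, and understates improvement at 8.

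**What to change.** State one baseline in the inclusion criteria, "Primary outcome", both relevant steps of "Recruitment process", "Primary outcome analysis" and the specimen section. Use it for both the change score and the covariate. Two statements must be replaced in any case: "the change in the number of days with moderate-to-severe headaches per menstrual cycle from the last menstrual cycle of the screening period" in the analysis section and "temporally aligned with the baseline headache diary data (derived from the same cycle after diagnosis confirmation" in the specimen section. Blood can still be drawn in the third screening cycle; only the claim about the diary baseline changes.

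- **Minimum:** apply the prevailing qualified-cycle mean in those two places.
- **Preferred:** define baseline as the mean moderate-to-severe headache days over all three screening cycles, with the 2–14 day rule used for eligibility only. In the scenarios run it lay as close or closer to later cycles, in either direction, and lost no precision.

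No new data are needed, since all three diaries are already required with at least 80% of daily entries completed in each cycle. The cost is a protocol amendment with ethics approval and a registry update. The preferred version also changes a definition that the authors state repeatedly. Some regression to the mean from the entry rule remains (up to about 0.3 days at an assumed mean of 3), so within-arm change should still be read with care.

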## Introduction

Menstrual migraine (MM) is a neurological disorder with a high prevalence that significantly impacts women’s lives; it is characterized by migraine attacks concentrated around the menstrual period. According to the International Classification of Headache Disorders, 3rd Edition (ICHD-3), MM can be subdivided into two distinct types: pure menstrual migraine (PMM, Appendix code A1.1.1) and menstrually-related migraine (MRM, Appendix code A1.1.2). PMM is defined as migraine attacks occurring exclusively between the second day before menstruation and the third day after menstruation in at least two of three consecutive menstrual cycles, with no attacks at other times during the menstrual cycle. MRM refers to attacks that occur both within this perimenstrual window and at other times of the cycle in at least two of three cycles (1). These two subtypes reflect fundamentally different temporal patterns of estrogen-withdrawal susceptibility and trigeminovascular sensitization. Epidemiological studies indicate that up to 60% of female migraineurs experience menstrual-related attacks, which are often more severe, longer in duration, and less responsive to conventional acute medications compared to non-menstrual migraines (2). These headaches substantially impair daily functioning, reduce quality of life, and contribute to absenteeism and socioeconomic burden (3).

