### Sample size

As this is a pilot feasibility study designed to estimate the effect size and variance of the primary outcome for a future definitive trial, no formal hypothesis-testing power calculation was performed. The sample size was determined with reference to previous multicenter randomized controlled trial of acupuncture for menstruation-related migraine (16, 17), which provided reference effect size estimates and variability data for this population. Based on the effect size reported in previous high-quality trials and clinical feasibility, we determined that 30 participants per group would provide a valid estimate of treatment response, variability, and retention (18). Assuming a 20% dropout rate during the trial, we planned to enroll 38 participants per group, with a total target sample size of 76. This sample size is sufficient to estimate key feasibility parameters and provides a preliminary basis for the design and sample size calculation of future confirmatory trials.

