#### Allocation of interventions

Participants who meet all eligibility criteria and provide written informed consent will be formally enrolled and assigned a unique study identification number. A computerized block randomization sequence with a 1:1 allocation ratio (Experimental Group: Control Group) will be generated by an independent statistician not involved in recruitment or intervention delivery, using random block sizes of 4 and 6. The allocation sequence will be concealed using sequentially numbered, opaque, sealed envelopes (SNOSE). Upon enrollment and completion of baseline assessments, the treating acupuncturist will open the next sequentially numbered envelope in the presence of the participant to reveal the group assignment. This process ensures allocation concealment.

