#### Handling of multiple comparisons

This trial includes one primary outcome and multiple secondary/exploratory outcomes. The primary outcome is designated as the primary endpoint for this pilot study and will be analyzed at a pre-specified two-sided alpha level of 0.05 without adjustment for multiplicity. Given the exploratory nature of this trial, all results—including the primary outcome—will be interpreted descriptively rather than as confirmatory evidence. No adjustment for multiple comparisons will be performed for any secondary or exploratory outcomes (headache intensity, functional impact, quality of life, acute medication use, heart rate variability indices, serum biomarkers, neuroimaging metrics). All these outcomes are designated as exploratory, and their results will be interpreted strictly as hypothesis-generating rather than confirmatory. This approach prioritizes sensitivity and hypothesis discovery over strict control of the family-wise error rate, and any positive findings will require confirmation in future adequately powered trials.

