#### Subgroup and sensitivity analyses

Pre-specified exploratory subgroup analyses will be performed based on menstrual subtype (PMM vs. MRM). Interaction tests between treatment group and menstrual subtype will be performed within the MMRM framework for the primary outcome, with results reported as exploratory (interaction *p*-values reported with 95% CIs). We acknowledge that the trial is not powered for formal subgroup comparisons, and all subgroup findings will be interpreted strictly as hypothesis-generating.

To account for potential expectation effects inherent in the open-label design, baseline “Credibility/Expectation Questionnaire” (CEQ) scores will be collected (19). In the primary analysis, CEQ scores will be included as covariates in the MMRM model to correct for potential expectation-related bias and improve the precision of treatment effect estimates. In addition, exploratory interaction terms (treatment × CEQ score) may be tested to investigate whether baseline expectations moderate treatment response; however, given the pilot nature of this trial, these analyses are strictly hypothesis-generating in nature and will be interpreted descriptively.

Sensitivity analyses will include: (1) PP analysis; (2) ITT analysis without imputation; (3) adjusting for potential baseline imbalances if any are observed.

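### PMM/MRM subtype is confirmed before randomisation but neither stratifies the allocation nor enters the primary model; adding it is a cheap, modest improvement

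*Protocol article*

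**What the plan says.** **Subtype is known in time.** Under Recruitment process, two independent neurologists confirm PMM or MRM from the three screening cycles, and only women with a confirmed diagnosis are randomised.

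**Subtype is treated as relevant.** The Introduction states: "These two subtypes reflect fundamentally different temporal patterns of estrogen-withdrawal susceptibility and trigeminovascular sensitization". Handling of missing data lists subtype among the auxiliary variables for imputation. Subgroup and sensitivity analyses makes it the subgroup factor, with a treatment-by-subtype interaction test in the primary-outcome MMRM. The Discussion lists the mixing of subtypes as a limitation that could affect how treatment effects are read.

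**Allocation.** Allocation of interventions describes "A computerized block randomization sequence with a 1:1 allocation ratio", with block sizes of 4 and 6. No stratification factor is named.

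**Primary model.** Primary outcome analysis gives an MMRM "with treatment group, time, and the interaction between treatment and time as fixed effects", with mean headache days over the qualified screening cycles as a covariate and a random intercept per woman. Subgroup and sensitivity analyses adds CEQ scores to the primary model. (The section on treatment credibility places them in sensitivity analyses; subtype is absent either way.)

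**Imbalance.** The third sensitivity analysis is "adjusting for potential baseline imbalances if any are observed". No variables or threshold are given.

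**The concern.** The protocol gives its own reasons to think subtype may matter, and the information is in hand when each envelope is opened. It is then used in secondary places (imputation, subgroup test) but not in the two places where it would protect the main estimate: the allocation list and the primary model.

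Baseline headache days may not carry all the information in subtype. By the Introduction's definitions, a PMM woman has attacks only around menstruation, while an MRM woman also has them at other times. Two women with the same baseline count can therefore differ in when their days fall.

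At stake is the reliability of the effect estimate and variance that this pilot is meant to hand to a later trial. With 76 women, a chance gap in subtype between arms is not rare, and the stated headline model would not correct for it.

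**Working it through.** **Inputs from the protocol article.** Sample size: 30 evaluable per group, 20% dropout, 38 per group and 76 in total. Allocation of interventions: 1:1, blocks of 4 and 6.

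**Inputs that are assumptions.** The article gives no PMM share, no subtype effect and no SD, and under Sample size says that "no formal hypothesis-testing power calculation was performed". I take a PMM share p of 20–50%, a residual subtype difference of 0.5, 1 or 2 days after baseline adjustment, and a residual SD of 2–3 days.

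**1. The plan's own figure.** 30 / (1 − 0.20) = 37.5, rounded up to 38 per group; 2 × 38 = 76. This reproduces.

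**2. Chance gap in PMM share.** The SD of the between-arm difference is sqrt(p(1 − p) × 2/38). The last two columns give the probability of a gap of 15 points or more, first by normal approximation and then by simulation of unstratified blocks of 4 and 6 (8,000 runs per scenario).

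| PMM share (assumed) | SD of gap | Normal | Simulated |
|---|---|---|---|
| 20% | 0.092 | 0.10 | 0.108 |
| 30% | 0.105 | 0.15 | 0.163 |
| 50% | 0.115 | 0.19 | 0.201 |

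An exact hypergeometric calculation with exactly 38 per arm and a fixed number of PMM women gives 0.082, 0.133 and 0.251. It differs because only certain gaps are possible with whole women. About 10–20% is a fair summary. At a PMM share of 10%, the simulated figure falls to 0.033. With blocks stratified by subtype, no simulated run reached even 10 points.

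**3. Shift in the contrast.** Shift = gap × residual subtype difference. For a 15-point gap:
- 0.15 × 0.5 = 0.075 day
- 0.15 × 1 = 0.15 day
- 0.15 × 2 = 0.30 day

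**4. Shift against the standard error.** With 30 per arm, SE = SD × sqrt(2/30) = 0.258 SD, ignoring any gain from the repeated cycles. For SD 2 the SE is 0.52 day, and a shift of 0.15 day is 0.29 SE. For SD 3 the SE is 0.77 day, and the shift is 0.19 SE.

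**5. Precision gained by adjusting.** If subtype explains a fraction r of the residual variance, the interval narrows by 1 − sqrt(1 − r). For r = 0.05 this is 2.5%; for r = 0.10 it is 5.1%. In SD units the 95% half-width goes from 1.96 × 0.258 = 0.506 to 0.493 or 0.480.

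To see which r is plausible, let g be the subtype difference divided by the SD within subtype; then r = p(1 − p)g² / (1 + p(1 − p)g²). A 1-day difference gives:
- SD 3: r = 0.017 (p = 20%) to 0.027 (p = 50%), a narrowing of 0.9–1.4%
- SD 2: r = 0.038 to 0.059, a narrowing of 1.9–3.0%

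A gain of about 1–5% covers these cases.

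**The case against.** The case against acting has several parts, and most of it stands.

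- **No bias.** A reader might infer that the primary comparison is biased. It is not. Under valid randomisation, imbalance in an omitted covariate is chance, and the confidence interval already allows for it.
- **Other covariates.** A reader might infer that baseline days are the only adjustment. The article also puts CEQ scores in the primary model, and baseline days may absorb part of any subtype difference.
- **Post-hoc adjustment.** A reader might infer that the main result depends on an adjustment chosen after seeing the data. The conditional adjustment is a sensitivity analysis beside a fixed primary model, and Blinding design keeps the statisticians on coded groups until the pre-specified analyses are done. The wording is loose, but its reach is limited.
- **Interaction test.** The planned treatment-by-subtype test would conventionally include a subtype main effect, so an exploratory subtype-conditional result already exists. The different timing of attacks relative to treatment is mainly an argument about effect modification. The interaction addresses that; a main effect does not.
- **Evidence of prognosis.** The Introduction speaks of temporal patterns, not of outcome. The article shows no prognostic difference beyond baseline days.
- **Subgroup size.** At a 20% PMM share there are about 15 PMM women, or 7–8 per arm even if perfectly split. Stratification evens the split but does not make the interaction test informative, and the article already says it is unpowered.
- **Context.** This is an exploratory pilot with descriptive p-values, and an unstratified block list with baseline adjustment is an acceptable design.

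What remains is narrow: the headline estimate omits a baseline factor that is already collected and that the protocol itself flags, and including it costs almost nothing.

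**Conclusion.** The point holds as a low-to-moderate, inexpensive improvement. Subtype is confirmed before randomisation and used elsewhere in the analysis, but it is absent from both the allocation sequence and the primary model. The validity of the trial is not in question.

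The chance of a 15-point gap is about 10–20% and rests on an assumed PMM share of 20–50%; it is lower if PMM is rarer. The shift of about 0.15 day rests on an assumed 1-day residual difference and amounts to roughly 0.2–0.3 of a standard error at an SD of 2–3 days. The precision gain of 1–5% is likewise assumption-based. The change is worth making because the trial exists to supply an effect size and variance for a later trial, and a pre-specified term settles the handling of subtype in advance.

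**What to change.** 1. Add subtype (PMM/MRM) as a fixed effect in the primary MMRM and in the secondary-outcome models, specified before unblinding.
2. If allocation has not begun, stratify the 1:1 sequence by subtype, with two lists and the same block sizes of 4 and 6. If it has begun, make the model change alone.
3. Keep the exploratory treatment-by-subtype interaction for the question of differential effect.
4. Keep the third sensitivity analysis for other baseline factors, but do not rely on it for subtype. Dropping it in favour of subtype alone would remove any check on other imbalances.

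The cost is one degree of freedom per model, a second set of envelopes, and possibly an incomplete block in each stratum. The sample size stays at 76. No new data are needed, since subtype is already recorded and already in the imputation model.
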